#### Measures of Parental Factors and Child Treatment Effects (Substudy 3)

To assess how parental distress, illness worry, and behavior impact the child’s overall treatment effects in various domains and treatment adherence, all participating parents and children or adolescents in the ICBT programs will answer extensive questionnaires before assessment (T1: baseline), halfway through treatment (T2: mid-treatment), at end of treatment (T3: end of treatment), and 3 months after the end of treatment (T4: follow-up; Figure 1). Furthermore, the number of completed treatment modules will be obtained from the treatment web page after the end of treatment. The specific measures to be used are shown in Table 2 and described subsequently.

**Table 2 table2:** Overview of questionnaires in substudy 3.

Outcome			Instrument	Time points and respondents^a^			
				T1	T2	T3	T4
**Parental factors**							
	Parental distress		SCL-8^b^ [44,45]	P	P	P	P
	Parental illness worries		HAPYS^c^ [46,47]	P	P	P	P
	Parental illness behavior		ARCS^d,e^ [48-50]	P	P	P	P
**Child treatment effects**							
	**Main measures**						
		Gastrointestinal symptoms	PedsQL Gastro^f^ [34]	C, A, P	C, A, P	C, A, P	C, A, P
		Pain intensity	Faces Pain Rating Scale – revised [51,52]	C, A, P	C, A, P	C, A, P	C, A, P
	**Additional measures**						
		Quality of life	PedsQL^g^ [53]	C, A, P	C, A, P	C, A, P	C, A, P
		Overall symptom load	CSSI^h^ [54]	C, A, P		C, A, P	C, A, P
		Depressive symptoms	MFQS^i^ [55,56]	C, A		C, A	C, A
		General anxiety	SCAS-S^j^ [57,58]	C, A, P		C, A, P	C, A, P
		Gastrointestinal anxiety	VSI^k^-short [35,59]	C, A	C, A	C, A	C, A
		Avoidance and control behavior	IBS-BRQ-C^l^ [36,60]	C, A	C, A	C, A	C, A
		Illness perception	B-IPQ^m^ [61,62]	C, A, P	C, A, P	C, A, P	C, A, P
		Illness worries	CIAS^n,o^ [63]	C, A	C, A	C, A	C, A
		Pain acceptance	CPAQ-A8^p,q^ [37]	C, A	C, A	C, A	C, A
**Other measures**							
	Adverse events		Yes or no, and open question			A, P	
	Treatment satisfaction		ESQ^r^ [64]			C, A, P	
	School absence		Hours past month	A, P	A, P	A, P	A, P
	Work absence		Days past month	P	P	P	P

^a^Time points; T1: baseline, T2: mid-treatment, T3: end-of-treatment, T4: follow-up; Respondents: C: child, A: adolescent, P: parent.

^b^SCL-8: Symptom Check List-8.

^c^HAPYS: The Health Anxiety by Proxy Scale.

^d^ARCS: Adult Responses to Children’s Symptoms.

^e^The monitor and protect subscales.

^f^PedsQL Gastro: Pediatric Quality of Life Inventory – Gastrointestinal symptoms.

^g^PedsQL: Pediatric Quality of Life Inventory.

^h^CSSI: Children’s Somatic Symptom Inventory.

^i^MFQS: Mood and Feelings Questionnaire Short.

^j^SCAS-S: Spence Children Anxiety Scale – Short.

^k^VSI: Visceral Sensitivity Index.

^l^IBS-BRQ-C: irritable bowel syndrome behavioral response questionnaire – Child-adapted short version.

^m^B-IPQ: Brief Illness Perception Questionnaire.

^n^CIAS: Childhood Illness Attitude Scale.

^o^The fear factor subscale.

^p^CPAQ-A8: Chronic Pain Acceptance Questionnaire – Adolescent Short Form.

^q^One question from the pain willingness factor, one from activity engagement.

^r^ESQ: Modified Experience of Service Questionnaire.

#### Parental Factors

Parental distress will be assessed by the Symptom Checklist-8, an 8-item subscale from the Symptom Checklist Revised-90, screening for emotional symptoms. Items are rated on a 5-point scale from 0 “not at all” to 4 “a whole lot,” with a total range from 0 to 32. Higher scores indicate more emotional distress [44,45].

Parental illness worries will be assessed by the Health Anxiety by Proxy Scale (HAPYS), a newly developed questionnaire assessing parents’ worries about their child’s health [46]. The questionnaire covers 26 items about health anxiety by proxy, rated on a 5-point scale (from 0 “not at all” or “never” to 4 “a whole lot” or “most of the time”), with a sum score range from 0 to 104. In addition, there are 6 items about the impact of the worries rated on a 4-point scale (from 0 “no” to 3 “yes, severely”), with a sum score range from 0 to 18. Higher scores indicate a high level of health anxiety by proxy and the impact of the anxiety, respectively. HAPYS is a valid measure of health anxiety by proxy with good psychometric properties, including high internal reliability and known-groups validity [47].

Parental illness behavior will be measured by the Adult Responses to Children’s Symptoms, which is originally a 29-item questionnaire [48]. In this study, 2 subscales (monitor and protect subscales) comprising 15 items will be used. Items are rated on a 5-point scale from 0 “never” to 4 “always” with a score range from 0 to 60. Higher scores indicate a higher degree of monitoring and protective responses [49,50].

#### Child or Adolescent Treatment Effects—Main Measures

Gastrointestinal symptoms will be assessed by PedsQL gastrointestinal symptoms [34]. This is a 9-item questionnaire assessing gastrointestinal symptoms related to functional or organic gastrointestinal diseases, during the past month, on a 5-point scale from 0 “never” to 4 “almost always.” Scores are reversed and transformed into a 0-100 scale, with high scores indicating greater quality of life. Pain intensity will be assessed by the Faces Pain Rating Scale – revised (FPS-R) [51]. The FPS-R score includes 6 pictures of faces, each showing an increasing amount of pain and scored on a 2-step scale between “no pain” (0) and “worst pain” (10). The scale is validated in children and adolescents and found to be sensitive to change [52].

#### Child or Adolescent Treatment Effects—Additional Measures

Quality of life will be measured by the 23-item PedsQL [53], which is a widely used questionnaire to assess quality of life during the past month in children and adolescents. Items are scored on a 5-point scale from 0 “never” to 4 “almost always.” Scores are reversed and transformed into sum scores between 0 and 100, with high scores indicating higher quality of life.

Overall symptom load will be assessed by the Children’s Somatic Symptom Inventory. It measures somatic symptoms during the last 2 weeks using 24 items, rated on a 5-point scale from 0 “not at all” to 4 “a whole lot,” with a range in scores from 0 to 96. High scores indicate a high symptom load. The questionnaire is found to be reliable and psychometrically sound for children and adolescents with abdominal pain disorders [54].

Depressive symptoms will be measured using the Mood and Feelings Questionnaire Short. It comprises 13 items rated on a 3-point scale from 0 “not true” to 2 “true,” with a range from 0 to 26, where higher scores indicate more depressive symptoms. The questionnaire is found reliable for evaluating depressive symptoms in both clinical and community populations of children and adolescents [55,56].

Anxiety levels will be assessed with 2 different questionnaires—the Spence Children Anxiety Scale Short (SCAS-S) [57,58] for general anxiety, and the Visceral Sensitivity Index-Children (VSI-C) [35,59] for gastrointestinal-specific anxiety. SCAS-S contains 19 items which are answered on a 4-point scale from 0 “never” to 3 “always,” with a total range from 0 to 57, where higher scores indicate higher anxiety levels. The questionnaire is designed for use in children and adolescents, and the short version is validated for screening of anxiety levels in children and adolescents [58]. The VSI-C is a shortened child-adapted version of the VSI for adults [35], with 7 items answered on a 6-point scale from 0 “strongly disagree” to 5 “strongly agree,” with a range from 0 to 42, where higher scores indicate more GI-anxiety. It has been found reliable and valid in children and adolescents with FAPDs [60].

Avoidance and control behavior will be assessed by the IBS-BRQ–Child-adapted short version with 11 items, which is an adapted version of the IBS-BRQ for adults [36]. Items are rated on a 7-point scale from 0 “never” to 6 “always,” with scores ranging from 0 to 66, where higher scores indicate more avoidance. It has been validated for children and adolescents with FAPDs [60].

Illness perception will be assessed by the Brief Illness Perception Questionnaire [61,62], which is a 9-item questionnaire where 8 items are answered on an 11-point scale, and 1 item is an open-ended question. The total score range is 0-80, with higher scores indicating more severe illness perception.

Illness worries will be assessed by the Childhood Illness Attitude Scale with 11 items from the fear factor [63]. The questionnaire is developed and validated for children and adolescents. Items are answered on a 3-point scale from 0 “never” to 2 “most of the time,” with a total score range from 0 to 22, and higher scores indicate more illness worries.

Pain acceptance will be assessed by 2 items from the CPAQ-A8 [37]. One regarding pain willingness and one regarding activity engagement. They are both answered on a 5-point scale from 0 “never true” to 4 “always true,” the item on pain willingness is reversed scored, and higher scores then indicate higher pain acceptance.

#### Other Measures

Parents will provide information about school absence (hours last month) for children (aged 8-12 years) and about their work absence (days past month). Adolescents will provide information about their own school absence (hours last month).

Adverse events will be assessed by adolescents and parents of children using a binary (yes or no) question and an open-ended question to describe the potential event in detail.

Treatment satisfaction will be assessed by the Modified Experience of Service Questionnaire [64], which is a 13-item questionnaire with 10 items scored from “not true” to “certainly true” and 3 free-text items. The total score range is 0-20 with higher scores indicating a better experience with the treatment.

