#### Exclusion Criteria

First, another medical or psychiatric disorder that better explains the symptoms. Second, severe child psychiatric or social problems (eg, high level of suicidal ideation, school absence of more than 40% during the past month, or ongoing substance abuse). Third, ongoing psychological treatment. Fourth, insufficient language or computer skills (patients and parents). Fifth, severe family problems (eg, child maltreatment, parental substance abuse or severe psychiatric illness, and custody fight).

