#### Design and Content of Treatment

The 4 distinct ICBT programs used in this study are targeted children (8-12 years), adolescents (13-17 years), and the parents of each group, respectively. The treatment lasts for 10 weeks and consists of 10 modules for children, adolescents, and parents of children (with a new module every week) and 5 modules for parents of adolescents (with a new module every other week). An overview of treatment content can be seen in Table 1. The programs include sections with videos, exercises, and quizzes designed to actively engage the child or adolescent in the treatment. Psychoeducation regarding FAPDs, detection of avoidance behavior, a brief mindfulness exercise called “SOL (Stop, observe, let go)” and graded repeated exposure exercises comprise some of the central components covered in the programs for both children and adolescents. The first modules of treatment introduce the above-mentioned concepts whereas later modules focus on repeated exposures. The purpose of “SOL” is Stopping, Observing how the stomach feels, and Letting go of the focus on the stomach and continuing with the activity. The parental programs emphasize supporting their child or adolescent’s exposure, decreasing attention to their child or adolescent’s abdominal symptoms, and prioritizing shared positive activities. Each module ends with planning of the homework assignments which are evaluated first thing in the next module.

**Table 1 table1:** Overview of the content of treatment for each module.

Module	Children (8-12 years)	Parents	Adolescents (13-17 years)	Parents
1	Introduction to the treatment format Psychoeducation on FAPDs^a^ (video) Mapping “stomach behaviors” (control, avoidance, safety) Setting treatment goals Homework: Self-monitoring	Introduction to the treatment format Positive attention Focus shift Mapping common parental behaviors Handling personal frustrations Homework: Focus shift, breaks, involving peers	Introduction to the treatment format Psychoeducation on FAPDs (video) Setting treatment goals Homework: self-monitoring	Introduction to the treatment format Focus on positive attention and shared moments Mapping common parental behaviors Homework: Shared positive moments

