### Data Analyses

In substudy 1, visual inspection analyses will be applied to demonstrate the effect of the intervention on all outcomes [71]. In addition, within-case effect size measurements will be calculated using Tau-U [72] and between-case effect sizes will be determined using hierarchical linear regression models to account for the serial dependency of data [73]. A randomization test will be applied to test differences in means for the baseline versus treatment, and baseline versus follow-up periods, respectively [74].

In substudy 2, participants’ descriptions reported in the recall phase of the BY-GIS task will be coded to their corresponding word or picture and category presented in the encoding phase (eg, picture-description “children and cake” coded as the birthday picture within the fun category). Coding for the first 20% of participants will be conducted by 2 independent raters ([name] and [name]). If the consensus rating exceeds 90%, 1 rater will code the remaining cases independently. A third and experienced rater ([name]) may be consulted to resolve potential disagreements. Baseline data will be analyzed descriptively and compared with (1) data from a healthy control group who performed the same experimental test [38], and (2) end-of-treatment data, exploring potential differences in the outcomes from the encoding, recall, and recognition phases using *t* tests or nonparametric tests, depending on data variability in the samples.

Baseline measures of interoceptive performance and metacognitive measures will be analyzed descriptively and compared with (1) measures from a healthy control group and (2) end-of-treatment measures, using *t* tests or nonparametric tests, depending on data variability in the samples.

In substudy 3, the potential moderation of parental factors on treatment adherence (number of completed modules) and main measure (gastrointestinal symptoms) for children or adolescents will be investigated using negative binomial regression and linear mixed models, respectively, adjusting for baseline parental distress, illness worries, and illness behavior, respectively.

In addition, the potential effect of treatment on these parental factors and all other child or adolescent measures will be analyzed using linear mixed regression models.

An experienced statistician will provide statistical support for all analyses.

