## Results

Recruitment of participants began in June 2022. Substudy 1 is finalized and expected to be published in 2025. Recruitment for substudies 2 and 3 is ongoing. By November 2024, 45 children and 24 adolescents have been included. Due to a skewed distribution in referrals, with a predominance of referrals on children, we continue to include children and adolescents until we have reached 30 adolescents. Inclusion is expected to be completed by January 2025 and data collection in March 2025.

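### School absence is set as hours in the past month with no school-time denominator, so holiday windows lower it at an unchanged absence rate (minor)

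*Protocol article*

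**What the plan says.** For the younger group, the Other Measures section of the protocol article says: "Parents will provide information about school absence (hours last month) for children (aged 8-12 years". For the older group it says: "Adolescents will provide information about their own school absence (hours last month". Table 2 repeats the unit as "Hours past month" and lists it at all four time points, under other measures rather than among the main or additional child treatment effects.

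The Exclusion Criteria put the same construct, over the same period, on a relative scale: "school absence of more than 40% during the past month".

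Timing follows treatment. Under Design and Content of Treatment, "The treatment lasts for 10 weeks", and the substudy 3 measures place the last questionnaire "3 months after the end of treatment (T4: follow-up; Figure 1". Neither refers to the school year. On enrolment, the Results section says "Recruitment of participants began in June 2022" and expects inclusion to be complete by January 2025.

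Data Analyses does not name school absence. It says that "all other child or adolescent measures will be analyzed using linear mixed regression models", with no denominator, offset or calendar term. The Discussion acknowledges that substudy 3 has no control group.

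**The concern.** Hours of absence in a month are bounded by the hours of school held in that month. When part of the window is holiday, the bound drops and recorded hours drop with it, whatever the child's symptoms do. T1 and T3 are at least 10 weeks apart, so one holiday can reduce one of the two windows and leave the other untouched.

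The direction depends on which window is hit. A low T1 makes the later visits look worse. A low T3 looks like benefit followed by relapse at T4. A low T4 looks like late or sustained benefit. T2 is exposed in the same way. Without a concurrent control group, nothing in the design cancels these shifts.

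At stake is how the change in school absence is read, for individuals and in summary. The Introduction names school absence among the burdens of these disorders, so the result is likely to attract interest.

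**Working it through.** The plan gives no figure on this point to reproduce. The check has four steps.

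**Inputs.** From the article: raw hours in the past month at T1 to T4; 10 weeks of treatment; T4 three months after treatment ends; recruitment from June 2022 to January 2025; no control group. Assumed, because the article does not give them: a window of 4.35 weeks, a year of 52.18 weeks, one summer holiday of H = 6 weeks (range 5 to 7), T3 11 to 13 weeks after T1, T4 13 weeks after T3, and enrolment dates evenly spread over the year.

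**1. Effect on one window.** Recorded hours = absence rate × hours of school held. Take a constant rate of 20% and, as an assumption, 100 school hours in a full month of four school weeks:

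| Holiday weeks in window | 0 | 1 | 2 | 3 | 4 |
|---|---|---|---|---|---|
| Recorded hours | 20 | 15 | 10 | 5 | 0 |

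The proportion is 20% in every column except the last, where no school was held and absence is undefined, not zero.

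**2. How many families are touched.**
- Any overlap, per visit: (H + 4.35)/52.18 = 10.35/52.18 = 0.198. T1 and T3 windows are separated by at least 11 − 4.35 = 6.65 weeks, so with H = 6 both cannot touch the holiday. T1 or T3: 2 × 0.198 = 0.40. For H = 5 and 7 the range is 0.36 to 0.44.
- At least half of the window inside the holiday, per visit: H/52.18 = 6/52.18 = 0.115. T1 or T3: 0.23 (range 0.19 to 0.27). T1, T3 or T4: 3 × 0.115 = 0.345, about 0.35 (range 0.29 to 0.40).
- At most a quarter of normal school time left, per visit: (6 − 4.35 + 0.5 × 4.35)/52.18 = 3.825/52.18 = 0.073.
- Window wholly inside the holiday, per visit: (6 − 4.35)/52.18 = 0.032.

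**3. Individual change.** Add assumed shorter breaks (two weeks in winter, three single weeks) and 1 to 4 weeks from T1 to treatment start, with no true change in absence. A T1 in mid-May then gives a T3/T1 ratio of recorded hours of 0.0 to 0.4. A T1 in mid-August gives 4.0 to 5.25.

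**4. Mean change.** With even enrolment, every visit date is also evenly spread, so the mean share of school held is the same at each visit. On the calendar of step 3 it is 1 − 11/52.18 = 0.79 at T1, T3 and T4. The calendar then contributes variance but no shift in the mean.

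The stated recruitment period covers June to January three times and February to May twice. If enrolment ran at a constant rate between those dates, with the holiday starting in late June and lasting 5 to 7 weeks, the mean share of school held is about 2 to 6% higher at T3 than at T1. That is a small spurious shift toward worsening. The actual monthly enrolment is not reported, and clustering of referrals could enlarge or reverse the shift.

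**The case against.** The strongest reply is that this is a condensed article. The questionnaire item, its help text and the analysis plan are not shown, so one cannot say that scheduled school time goes uncollected, and the handling of holiday windows may be settled elsewhere. That stands to this extent: the claim can only be that the article defines the measure in raw hours and states no denominator. It does not dispose of the point, because the unit is something the article itself fixes.

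It can also be said that a percentage for screening and hours for describing burden do not contradict each other. That is right. The exclusion rule shows only that a relative scale is already in use for this construct.

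A reader might infer that holidays produce near-zero absence as a rule. They do not. That needs a holiday filling most of the month, about 7% of windows per visit on the assumptions above; a break of one or two weeks lowers recorded hours by about 25 to 50%. Nor does any start near summer mislead: on the calendar of step 3, a T1 in mid-June gives a T3/T1 ratio of only 0.73 to 1.0.

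A reader might also infer that the mean change is systematically biased. The documents do not support that, since they do not report how enrolment was spread over the year, and even enrolment gives no shift.

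Finally, importance is low. School absence is listed among other measures, the Data Analyses section never names it, and its inclusion in the linear mixed models is a plausible reading rather than a statement. No sample size or main conclusion rests on it, and the Discussion already calls substudy 3 explorative and urges caution on clinical effect. All of that stands and sets the weight of the point.

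**Conclusion.** The point holds as a minor one. As the article defines it, recorded school absence depends on how much school was held in the window as well as on the child's absence rate. With an assumed 6-week summer holiday and even enrolment, about two families in five have T1 or T3 touched, and just under one in four have at least half of one of those windows in holiday, which at least halves recorded hours at an unchanged rate. The consequence in this uncontrolled design is added noise and misread individual change. Bias in the mean change needs uneven enrolment over the year and cannot be claimed from what is reported. All these sizes rest on the assumed holiday length, visit spacing and enrolment pattern. The general mechanism does not.

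**What to change.** For all families, including those who have finished, derive the number of school days in each past-month window from the questionnaire completion date and the school calendar. Analyse absence relative to school time held, in one of two ways:
- as a proportion, converting school days to hours with the usual school hours per day for the child's class level; or
- as hours with school time as an offset, which calls for a count model with a log link, such as the negative binomial model already planned for completed modules, rather than a linear mixed model.

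Set windows with no school days to missing, not zero. State this in the analysis plan before the data are analysed, and report enrolment by calendar month so that readers can judge any seasonal imbalance.

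A new questionnaire item on scheduled hours would now reach few windows, since 45 children and 24 adolescents were already included by November 2024, and it would mix two ways of obtaining the denominator. The calendar lookup treats everyone alike.

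The cost is some data work and the loss of a few windows: about 3% per visit for the 6-week holiday, from step 2. No visits are added and nothing changes for participants.

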## Methods

### Study Design

The study includes 2 recruitment phases. The first phase concerns a single case experimental design (SCED) study (substudy 1) with a total of 12 patients (6 children and 6 adolescents, respectively). The second phase concerns an open pilot study on cognitive biases and interoceptive accuracy (substudy 2) with a total of 60 patients (30 children and 30 adolescents, respectively).

Consequently, a total of 72 children and adolescents, along with a corresponding number of parents, will undergo ICBT for FAPDs throughout the entire study. Parental distress and illness worries will be assessed before, during, and after the treatment in all included parents (substudy 3; Figure 1).

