### Data Collection and Management

The DSQ, the BY-GIS task, and questionnaires are set up in REDCap (Research Electronic data capture; Vanderbilt University) [70], hosted by Aarhus University, and distributed through SMS text message or email. REDCap is a secure, web-based software platform designed to facilitate data capture for research studies.

For the DSQ (substudy 1), a text message reminder will automatically be sent through REDCap 2 hours after the initial SMS text message. If the DSQ is not completed 2 days in a row, a research assistant will contact the family by phone. For the BY-GIS task (substudy 2) and the extensive questionnaire (substudy 3), REDCap will generate automatic email reminders 24, 48, and 72 hours after the initial email if they are not completed. If there is no response after 7 days, a research assistant will contact the family by phone.

The interoception task in substudy 2 will take place at the Center of Functionally Integrative Neuroscience at Aarhus University Hospital in a behavioral testing room, and data will be stored in REDCap.

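### The only adverse-event question is scheduled at end of treatment (T3), so events in the 3 months to follow-up are never asked about and a family missing T3 gives no adverse-event answer

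*Protocol article*

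**What the plan says.** Under Other Measures the article says that "Adverse events will be assessed by adolescents and parents of children using a binary (yes or no) question", with an open-ended question to describe any event. That sentence gives no time point.

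The time point comes from Table 2, block Other measures. The adverse-event row ("Yes or no, and open question") has an entry for adolescents and parents in the T3 column only; T1, T2 and T4 are blank. The table footnote defines the columns as "T1: baseline, T2: mid-treatment, T3: end-of-treatment, T4: follow-up".

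The section on substudy 3 measures says that all participating parents and children or adolescents answer questionnaires before assessment, "halfway through treatment (T2: mid-treatment), at end of treatment (T3: end of treatment), and 3 months after the end of treatment". Under Design and Content of Treatment, "The treatment lasts for 10 weeks". Under Study Design, "a total of 72 children and adolescents, along with a corresponding number of parents, will undergo ICBT".

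On missing questionnaires, Data Collection and Management plans email reminders at 24, 48 and 72 hours, and then: "If there is no response after 7 days, a research assistant will contact the family by phone".

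**The concern.** The treatment is built on graded exposure that becomes harder over the modules, and substudy 3 has no control group. Any statement about harm therefore rests on how completely events are collected.

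The stated schedule has two gaps:

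- **After T3.** Benefit is measured at the 3-month follow-up, but adverse events are not asked about there. The period after therapist support ends has no solicited adverse-event data.
- **At T3.** All adverse-event information from a family depends on one response. If worsening makes a family stop and then leave T3 unanswered, the families lost are not a random subset. An adverse-event proportion among T3 responders could then be too low.

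This is a schedule that the article fixes, not a detail left to a fuller document. The T4 questionnaire exists and goes to the same respondents.

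**Working it through.** The article gives no figure for adverse events (no expected rate, precision or response rate), so there is nothing to reproduce. The check is of the schedule, followed by simple arithmetic.

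**1. Is T3-only a real entry or a broken table?** Rows from the Other measures block of Table 2:

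| Row | T1 | T2 | T3 | T4 |
|---|---|---|---|---|
| Adverse events | – | – | A, P | – |
| Treatment satisfaction | – | – | C, A, P | – |
| School absence | A, P | A, P | A, P | A, P |
| Work absence | P | P | P | P |

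(C child, A adolescent, P parent.) The two absence rows are filled at all four points, so the blanks are not a fault of the whole block. The adverse-event item follows the pattern of treatment satisfaction, which is naturally a once-only, end-of-treatment question.

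**2. Share of the observation period after the only question.** Treatment is 10 weeks. Follow-up is 3 months later, taken as 12 to 13 weeks.

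- 12 / (10 + 12) = 12/22 = 54.5%
- 13 / (10 + 13) = 13/23 = 56.5%

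**3. Families with no adverse-event answer.** Planned number treated: 72. T3 non-response *d* is not given, so 0 to 30% is assumed. Families without an answer = 72 × *d*. If no event is reported, the proportion of families with an event can lie anywhere between 0 and (families without an answer)/72, with no assumption about who is missing.

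| Assumed *d* | Answer | No answer | Range for true proportion if none reported |
|---|---|---|---|
| 0% | 72 | 0 | 0% |
| 10% | 65 | 7 | 0 to 7/72 = 9.7% |
| 20% | 58 | 14 | 0 to 14/72 = 19.4% |
| 30% | 50 | 22 | 0 to 22/72 = 30.6% |

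The last column gives logical limits, not estimates. It leaves sampling error aside and takes each T3 answer as complete for the period up to T3. It shows that the answer depends on the unanswered forms, whose number the article does not give.

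**4. Number treated.** The 72 is the plan. Results reports 45 children and 24 adolescents by November 2024, with both groups continuing until there are 30 adolescents. If the 30 is counted on the same basis as the 24, the final number is at least 45 + 30 = 75. This scales step 3 slightly and leaves step 2 unchanged.

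**The case against.** Several objections have force.

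- **Harm is not invisible elsewhere.** Gastrointestinal symptoms, pain intensity, quality of life and school absence are scheduled at T2 and T4 as well. Depressive symptoms, general anxiety and symptom load are scheduled at T3 and T4. The 12 substudy 1 participants also rate symptoms daily. A reader might infer that a family missing T3 contributes no harm data at all; the article does not support that. What it lacks is an adverse-event answer. None of these scales is designated a harm measure, and none captures an unexpected event, which is the purpose of the open question.
- **T3 is not limited to completers.** A reader might infer that the count is confined to families who finish treatment, is survivor-biased, or rests on 10-week recall. The article says that all participants answer the questionnaires, ties none of them to module completion, chases non-response by email and phone, and states no recall window. Informative loss is plausible, not shown.
- **Smaller numbers alone matter little.** With zero events, the one-sided 95% upper bound 1 − 0.05^(1/n) is 4.1% at n = 72 and 5.0% at n = 58. That change reflects only an assumed smaller n. It would apply to any T3 item and does not measure the effect of asking only once.
- **A fuller protocol may hold other routes.** Therapists give written feedback after each module, and spontaneous or therapist-recorded reports may be covered in a document not shown. That would soften the point about families missing T3. It would not put a question into T4.
- **Safety is not among the three aims**, and the article describes no adverse-event analysis. This limits the importance of the point.
- **It is late.** With 69 participants included by November 2024, many families are past T2.

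**Conclusion.** The point stands in limited form. As scheduled, adverse events are solicited once, at T3. About 55% of the time from treatment start to T4 (12 to 13 of 22 to 23 weeks) lies after that question and is never covered by another. A family that does not answer T3 gives no adverse-event answer in the schedule shown. This would be about 7 to 22 of 72 families at an assumed 10 to 30% non-response, a range the article neither supports nor excludes.

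The direction of any bias is a reasonable inference: too few events, if worsening leads to stopping and to non-response. Its size cannot be derived.

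The conclusion rests on Table 2 being read as laid out, and on no further adverse-event route being described in the article. It does not touch the main aims. It limits what any safety statement from the study can claim.

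**What to change.** 1. Add the existing yes/no and open-text item to the T4 questionnaire, and to T2 for families not yet past it, with the same respondents.
2. Ask the item in the phone call already planned after 7 days of non-response, so that a family that will not complete the form can still answer this question.
3. In the report, give the number of treated families with at least one adverse-event response beside any event count. State that events after T3 were not solicited for families who passed T4 before the change.
4. While editing, reconcile the respondents. Table 2 lists adolescents and parents, whereas the text names adolescents and parents of children, so it is unclear whether parents of adolescents are asked.

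**Cost.** One short item in forms already sent, a line in the call script, and possibly a minor ethics notification. Item 3 needs no new data.

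**Limit.** Coverage will be incomplete because most participants are already enrolled. A family included in January 2025 reaches T4 after 10 weeks plus 3 months, about mid-2025, yet the Abstract puts final data collection in April 2025 and Results in March 2025. The sponsor should confirm that T4 will be collected for late entrants, since they are the ones an added T4 item would mainly reach.
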